### Qualitative phase: Study instrument and focus group discussion

Upon identifying the samples for the quantitative study, a subsample will be selected among them to participate in the Focus Group Discussion (FGD). As a rule of thumb, 10% of the estimated sample size for the quantitative study will be selected to join the FGD. Meanwhile, the number of participants participating in the FGD will be equally distributed across the four districts. A semi-structured questionnaire will be used for the FGD respondents to share their thoughts and opinions. The qualitative study aims at identifying and better understanding the social factors related to their delayed presentation to the healthcare centres.

Six components will be explored during the discussion, namely demographic, socio-cultural, and health-seeking behaviours, social support and resources, previous knowledge and experience with illness, as well as treatment pathway. The guide will be revised in subsequent FGD to probe any new emerging themes. In all the FGDs, the discussions will be audio-recorded and transcribed verbatim after that. The concept of theoretical saturation will be used to ensure no new conceptual information emerges from the discussion. Subsequently, all the findings from the qualitative phase will be transcribed and coded. The identification, coding, and categorisation of meaningful patterns into themes and subthemes will be conducted to facilitate the construction of a structured questionnaire for the quantitative study. Interview transcripts will be analysed using NVivo (Version 12).

### Quantitative phase: Instrument development

A structured questionnaire will be constructed based on the themes identified in the qualitative study and a review of several studies in the literature. Operational definitions will be developed based on the themes obtained. The questionnaire will undergo content validity by three field experts. Then, it will be distributed to ten healthcare professionals for face validity assessment. Necessary modifications will be made based on the comments received. The final questionnaire will then be translated into the local language, Bahasa Malaysia, and pre-tested on 30 TB patients from selected hospitals and health clinics for the reliability or internal consistency. Based on the field experts’ opinions and pilot testing, potential ceiling and floor effects from the questionnaire items that may affect accurate data interpretation will be prevented.

For the quantitative phase, a cross-sectional study using the developed questionnaire will be distributed to the patients identified through the PPS technique at all selected hospitals and health clinics in all four districts. Finally, the data obtained from both qualitative and quantitative approaches will be combined to provide a more robust assessment of the study. The qualitative findings from the viewpoints of the participants in FGD will facilitate the interpretation of the study results, whereas the quantitative results will provide a better understanding of the study objectives and research questions [22]. An expert panel will be engaged to construct the social epidemiology framework model for delayed presentation of TB.

The research design in this study offers the strengths of both quantitative and qualitative approaches, thus providing a more robust outcome for this study. A mixed-method research design can also broaden the dimension and scope of the study [22]. Table 1 shows the research matrix and Fig 1 presents the overall research design of this study according to each research question.

**Fig 1 pone.0266746.g001:**
[figure not shown]
Research design of the different study phases.

**Table 1 pone.0266746.t001:** Research matrix.

RESEARCH OBJECTIVES	QUANTITATIVE	QUALITATIVE
To describe the incidence of TB in Selangor and the health-seeking behaviour (timeline between the onset of symptoms to the first presentation to the healthcare facility and medical visit) among the patients.	√	√
To describe the social epidemiological characteristics (socio-demographic and socio-cultural) of the TB patients in Selangor.	√	
To determine the types of health provider barriers that are prevalent in Selangor.	√	√
To determine the association between health-seeking behaviour and social epidemiological factors (socio-demographics and socio-cultural) as well as health provider barriers.	√	
To investigate the key factors that contribute to delayed presentation of TB patients.		√
To construct a predictive social epidemiology framework for the identification of delay in seeking treatment among TB patients in Selangor.	√	√

### Ethical consideration

This study will involve two key ethical principles, namely honesty and respect for human rights [22]. Since adults with TB disease will be the study participants, certain ethical questions need to be addressed. The confidentiality and safety of respondents must be guaranteed. Therefore, informed consent will be obtained from the participants in survey questionnaires. The researcher shall provide important information and purpose about the study with a cover letter on the questionnaire to the participants before obtaining their informed consent. This study protocol has been approved by the Research Ethics Committee UKM (JEP-2020-589) and the Medical Research & Ethics Committee Ministry of Health Malaysia (NMRR-20-1595-55723).

### Management

The researchers will ensure the protection of participants’ anonymity. Meanwhile, data concerning people will be kept confidential to ensure that their identities and any form of identifying information are protected. A coding system will be employed to represent the clinical records, research instruments or any used documents containing participants’ data. Hence, no participants’ names will be revealed even when submitting the information to sponsors or regulatory institutions. Both the participants’ records and the coding system will remain confidential and accessible only by the researchers. Consent forms will be provided in two copies to be signed by the participant and the researcher. A secure location containing a single folder will be dedicated to storing all the files.

The participant will not incur any personal expenses during the study; hence, all evaluations will be free. Additionally, no financial compensation or incentives will be given for participation. Any additional expenses will be covered by the research budget. Meanwhile, participation is completely voluntary, and there is no implication in the patient’s medical follow-up for nonparticipation. Upon signing the consent form, participants can withdraw from the study at any time, if desired, without any consequences related to their treatment or follow-up at the hospital. The anticipated research results may be published in a journal article or presented at meetings; nevertheless, the participants’ identities will remain confidential. Most importantly, this research poses no risk to the participants.

### Quality control measures

Several important methodological resources will be used to ensure quality data collection and minimise bias in the study. This includes the mixed-method study design, inclusion and exclusion criteria, random sampling technique and randomisation process. The principal researcher will collect all the data during the FGD, whereas additional enumerators will assist with the data collection during the quantitative phase. These enumerators will participate in distributing the questionnaire during the pilot test for them to get familiarised with the study instrument. Meanwhile, during the quantitative phase, the principal researcher will ensure that enumerators are following the survey protocol. Participants would be assisted while completing the questionnaire if necessary to minimise missing data. Another quality control measure is the principal researcher’s role by reviewing the completeness and quality of data in the returned questionnaires.

### Data analysis

For the qualitative phase, interview transcripts will be analysed using NVivo (Version 12). The software will be used to develop the main themes and sub-themes from the focus group discussion. Meanwhile, the quantitative data will be analysed using the IBM SPSS for Windows (version 25.0, Armonk, NY. IBM. Corp.). Cronbach alpha values will be computed from the reliability test to assess the reliability and to ensure the internal consistency of the questionnaire items. Cronbach alpha values of more than 0.7 will be accepted as reliable. Descriptive statistics will be used to summarise the data regarding participants’ socio-demographic characteristics, socio-cultural factors, health-seeking behaviours, and delayed presentation of TB.

The independent variable in this study is the delayed presentation of TB (measured in time: days and weeks), hence, the data will be subjected to normality tests using the level of kurtosis and skewness. Means and standard deviations will be presented for normally distributed data, whereas if the assumption of normality is not met, median and interquartile range will be presented. The cumulative incidence of TB will be estimated based on the number of new cases of TB divided by the total number of participants at risk. Determinants of delayed TB presentation will be analysed using multiple regression models. All parameter estimates will be computed at a 95% confidence interval, and statistical significance will be reported at *p* < 0.05. Lastly, a measurement model and structural modelling analysis will be performed using SmartPLS 3.0.

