## Research questions

Due to the high incidence of TB infections in the state of Selangor, the research aims to answer the following questions:

What is the incidence rate of TB in Selangor?What is the distribution of socio-demographic factors among the TB patients in Selangor?What is the distribution of socio-cultural factors among the TB patients in Selangor?What is the distribution of health-seeking behaviours among the TB patients in Selangor?What are the barriers faced by healthcare providers that can influence the TB diagnosis?How do the socio-demographic, socio-cultural, and health provider factors interact to influence health-seeking behaviours among TB patients?

To answer the aforementioned research questions, this research focuses on the identification of risk factors for delayed presentation of TB in Selangor.

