## Methods

### Study design and study area

This study will adopt a mixed-method research design. We will combine quantitative and qualitative approaches to obtain comprehensive results regarding the research questions [22]. The exploratory sequential mixed methods design will be conducted for the data collection. Data collection will be performed among patients who have been diagnosed with TB using chest X-ray and sputum smear microscopy. Four districts with the highest recorded cases in the state of Selangor will be selected as study locations. The sampling frame will be determined from the MyTB system database and patients fulfilling the inclusion criteria will be identified as sampling units. Thereafter, they will be categorised based on the four districts to ensure there are respondents from each district.

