### Study population

The study population will comprise TB patients in the state of Selangor.

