### Inclusion criteria

The following inclusion criteria will be used in recruiting the study participants:

Confirmed TB patients that were diagnosed using chest X-ray and sputum smear microscopy.TB patients from districts with the highest recorded cases in SelangorInformed consent to participate in the study

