### Exclusion criteria

The exclusion criteria are as follows:

Suspected or unconfirmed TB patients.TB patients from districts with low recorded cases of TB in SelangorDecline to provide informed consent to participate in the study

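### The written cumulative-incidence estimator cannot give the incidence of TB in Selangor, because its denominator is study participants and every participant is already a confirmed case

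*Protocol article*

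**What the plan says.** The first item under Research questions asks: "What is the incidence rate of TB in Selangor". The first row of Table 1 begins: "To describe the incidence of TB in Selangor and the health-seeking behaviour", and continues with the time from symptom onset to first presentation.

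The Data analysis section gives the only estimator for this question. Cumulative incidence is to be "estimated based on the number of new cases of TB divided by the total number of participants at risk".

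Other sections of Methods fix who the participants are:

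- Study population: "The study population will comprise TB patients in the state of Selangor".
- Inclusion criteria: "Confirmed TB patients that were diagnosed using chest X-ray and sputum smear microscopy".
- Exclusion criteria: "Suspected or unconfirmed TB patients".
- Study design and study area: "The sampling frame will be determined from the MyTB system database and patients fulfilling the inclusion criteria will be identified as sampling units". Recruitment is confined to the four districts with the most recorded cases.
- Instrument development (quantitative phase): the survey is cross-sectional.

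No section names a resident or census population as a denominator for the incidence analysis.

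**The concern.** Incidence needs a group that is free of the disease at the start, or a resident population that stands in for one, and a count of new cases arising in it over a stated period. This study enrols people who already have TB and surveys them once. The denominator in the Data analysis section therefore conflicts with the eligibility rules.

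The estimator is written out, so this is not a detail left for a later analysis plan. An analyst who followed it would report a number labelled cumulative incidence that says nothing about how often TB arises in Selangor. Research question 1 would then be answered with a figure that has no such meaning.

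**Working it through.** The protocol states no incidence result and no final sample size, so there is no figure to reproduce. The check is to apply the written rule to the population that the protocol defines.

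**Inputs**

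- Rule (Data analysis): CI = new TB cases / participants at risk.
- Participants (Study population, Inclusion criteria, Exclusion criteria): n people, all with confirmed TB.
- Design (Instrument development): one cross-sectional survey with no follow-up for onset.
- Background (the section on why the study is important): 5,071 TB cases in Selangor in 2018; population more than 6.4 million; nine districts, of which four are studied.

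**Applying the rule under each reading**

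1. *All participants count as new cases, and all form the denominator.* CI = n / n = 100%, whatever n is.
2. *New means not previously treated, and all participants form the denominator.* CI = (s × n) / n = s, the share of new cases in the sample. The protocol gives no value for s. If s is assumed to lie between 80% and 95%, the result is 80% to 95%. This describes the case mix of the sample.
3. *At risk is read strictly as free of TB at the start.* The denominator is 0 and the ratio is undefined.

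None of these involves the residents of Selangor or a period of time, so none is an incidence.

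**A population-based figure, for scale only**

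5,071 / 6,400,000 × 100,000 = 79.2 per 100,000, or 0.079%, for 2018.

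This is rough and probably high. The population is given as more than 6.4 million, and the 5,071 are described as TB cases, not as new cases. It also covers the whole state, while the survey covers four of nine districts. Reading 1 exceeds it by a factor of 100 / 0.0792, about 1,260, but that ratio applies to reading 1 alone and is not a measured bias.

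**Would changing only the denominator be enough?** No. The number of surveyed patients is set by the sample-size calculation and by consent. Sampled patients over residents would still not count the cases that arose. Both numerator and denominator must come from outside the survey.

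**The case against.** **The result is not necessarily 100%.** A reader might infer that the rule returns 100% by construction. The documents do not support that as a certainty. It is one of three readings, and the text does not say that the new cases in the numerator are survey participants. This stands, and the point should not be headed by the 100%. It does not rescue the estimator: a case count from outside the survey, divided by the number surveyed, would change with the chosen sample size and would still not be an incidence.

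**Participants at risk may have been meant as the resident population.** That is the charitable reading, but the text does not say it, residents are not participants, and no population source is named. If it was the intention, the sentence still needs correcting.

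**Table 1.** A reader might also infer that the qualitative tick in the first row commits the focus groups to estimating incidence, and that it should be removed. That does not hold. The row joins incidence with health-seeking behaviour under one pair of ticks, and the focus group section lists health-seeking behaviours and treatment pathway among its six topics. The second half of the objective explains the tick.

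**The defect is peripheral.** Incidence does not appear in the Objectives section or among the aims in the abstract. The Research questions section closes by placing the focus on risk factors for delayed presentation. The sample-size method rests on studies of delay, and neither the regression nor the structural model uses the incidence figure. This stands and lowers the severity.

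**The remedy assumes data.** The protocol describes MyTB only as a sampling frame. That aggregate counts and matching district populations can be obtained is an assumption. This stands too, so the fix needs an alternative that requires no outside data.

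**Conclusion.** The concern holds as a contradiction between the written estimator and the eligibility and design sections. With confirmed cases only and no follow-up for onset, the ratio is 100%, the new-case share, or undefined, and in no case the incidence of TB in Selangor. This rests on the text alone. The 80% to 95% range is an assumption, and 79 per 100,000 only indicates scale.

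The estimator also falls short of the question in two further respects: research question 1 asks for a rate for the whole state, whereas the rule gives a proportion among patients from four of nine districts.

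The severity is moderate. One descriptive research question and half of one Table 1 objective cannot be answered as planned. A reader might take this as a threat to the whole study, but the analyses of delay do not depend on it.

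**What to change.** Replace the sentence in the Data analysis section with a notification rate: all new TB cases notified in a stated calendar year (registry totals, not the survey sample), divided by the resident population of the same area, per 100,000. State the area so that numerator and denominator match: either the four study districts, with research question 1 and Table 1 limited to them, or all of Selangor, with counts from all nine districts. Name the source of the population figures.

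If aggregate counts are not available, drop incidence from research question 1 and from the first Table 1 objective, and delete the sentence. The health-seeking half of that objective then remains. In either case keep the qualitative tick in that row.

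The cost is small. The first option takes one reworded sentence, an aggregate registry count and a population figure, provided that these can be obtained. The second takes only edits to the text. Neither adds participants or changes recruitment, the questionnaire or the delay analyses.

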### Timeline

All participants for the qualitative phase have been recruited, and the study is expected to be completed by April 2022. Meanwhile, participants’ recruitment for the quantitative phase will commence in March 2022. The data analysis will be performed by August 2022, and the research article will be completed by October 2022.

## Conclusion

Based on the published literature, there is limited research on the social factors and their association with delayed presentation among TB patients. With the increasing prevalence of TB in Malaysia, our proposed research will be vital because it can provide an overview of the collective effects of social development and environmental factors on TB. It can also be used to evaluate if the social disadvantages outweigh the positive effects of overall growth in Malaysia. Furthermore, this study will shed insights into the social factors associated with the delayed presentation of TB so that targeted strategies can be implemented to reduce the local incidence of TB.
